**Methods:**

The clinical study (DRKS00026624) includes two randomized controlled intervention trials with parallel groups, for patients with elective cardiac catheterization and practitioners at the catheterization lab, in two clinic sites of the Ernst-von-Bergmann clinic network in Brandenburg, Germany. Both groups received different interventions for stress management. The intervention for patients comprises a psychoeducational video with different stress management technics and additional a standardized medical information about the cardiac catheterization examination. The control condition includes the in hospitals practiced medical patient education before the examination (usual care). Primary and secondary outcomes are measured by physiological parameters and validated questionnaires, the day before (M1) and after (M2) the cardiac catheterization and at a postal follow-up 6 months later (M3). It is expected that people with standardized information and psychoeducation show reduced complications during cardiac catheterization procedures, better pre- and post-operative wellbeing, regeneration, mood and lower stress levels over time. The intervention for practitioners includes a Mindfulness-based stress reduction program (MBSR) over 8 weeks supervised by an experienced MBSR practitioner directly at the clinic site and an operative guideline. It is expected that practitioners with intervention show improved perceived and chronic stress, occupational health, physical and mental function, higher effort-reward balance, regeneration and quality of life. Primary and secondary outcomes are measured by physiological parameters (heart rate variability, saliva cortisol) and validated questionnaires and will be assessed before (M1) and after (M2) the MBSR intervention and at a postal follow-up 6 months later (M3). Physiological biomarkers in practitioners will be assessed before (M1) and after intervention (M2) on two work days and a two days off. Intervention effects in both groups (practitioners and patients) will be evaluated separately using multivariate variance analysis.

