**Discussion:**

This study evaluates the effectiveness of two stress management intervention programs for patients and practitioners within cardiac catheter laboratory. Study will disclose strains during a cardiac catheterization affecting both patients and practitioners. For practitioners it may contribute to improved working conditions and occupational safety, preservation of earning capacity, avoidance of participation restrictions and loss of performance. In both groups less anxiety, stress and complications before and during the procedures can be expected. The study may add knowledge how to eliminate stressful exposures and to contribute to more (psychological) security, less output losses and exhaustion during work. The evolved stress management guidelines, training manuals and the standardized patient education should be transferred into clinical routines.

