### Outcomes

The primary outcomes for patients are reduced complications and less sedative medication during CC (documented by nurses at the CC lab), and less tension/strain (physiological parameters like pulse, blood pressure, heart frequency), perceived stress (PSS) and better mood (POMS) measured by established and validated self-report questionnaires. Further secondary outcomes for patients are better pre- and post-operative wellbeing, chronic stress (TICS), depression and anxiety (HADS), panic disorder, psychosocial functioning (PHQ-9), life events (ILE), general health (SF-12), satisfaction with health and sleep (41). Additionally, patients are asked about their life style, socioeconomic status and satisfaction about the intervention. At the CC lab, nurses document the behavior of the patients during the cardiac catheterization (agitation, duration of hospital stay, tranquilizer/sedativa use, and level of information) and the number of complications occurred during the procedure. The primary outcomes for practitioners—perceived (PSS) and chronic stress (TICS)—are measured by established and validated self-report questionnaires. Additionally, stress load and recovery are assessed by physiological measurements: circadian profile of HRV (42–44), saliva cortisol (45), alpha-amylase (46) and lysozyme on two working/lab days and two days off as well as the following night, prior to and after the intervention, respectively. The HRV measurements base on beat-to-beat R-R intervals and comprises outcomes for the total activity of the autonomic nervous system [standard deviation of RR intervals (SDNN)], parasympathetic function [root mean sum of squared distance (RMSSD)] and stress load and recovery (number and percentage of R-R intervals lower or >50 msec). Saliva samples are taken on nine defined time points during the day (immediately after awakening, 30, 45, 90, 150 min after awakening, before lunch, 4 p.m., before dinner and going to bed) on a working/lab day and day off. Weight and mood (POMS) are assessed simultaneously as control variables. The practitioners are further asked about vital exhaustion (VE), anxiety and depression (HADS), tension, effort-reward imbalances (ERI), social support (BSSS), satisfaction with health and sleep (41) as well as life style, socioeconomic status, expectations and adherence (barriers) to the intervention program.

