### Statistical Analysis

All statistical analyses will be performed using SPSS. The data of the practitioners will be mainly analyzed descriptively due to the small sample size. Interferential statistics will be used to identify group differences. A comparison with norms of the German general population will be performed to assess the stress of the practitioners in the cardiac catheter laboratory. Baseline and post-interventional physiological data like circadian profile slopes of HRV and derived indicators (SDNN, RMSSD, number and percentage of R-R intervals lower or >50 msec) as well as saliva cortisol, alpha-amylase and lysozyme measurements will be compared on an intraindividual level. The data of the patients will be analyzed according to a multivariate variance analysis (between-subject factor: intervention group vs. control group). Sociodemographic data, sedative medication, adherence to the intervention will be implemented as control variables or stratification variables for subgroup analysis. Statistical significance is set at *p* < 0.05 (two-sided) and effect sizes will be reported.

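### The practitioner trial has two unranked primary outcomes at an unadjusted 0.05 and conflicting statements of its deciding analysis; if either outcome may carry the effectiveness claim, false-positive risk is about 7% to 9.75%

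*Protocol article*

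**What the plan says.** All references are to the protocol article.

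- **Outcomes.** "The primary outcomes for practitioners—perceived (PSS) and chronic stress (TICS)—are measured by established and validated self-report questionnaires". The two are listed side by side. The biological measures follow in a separate sentence: "Additionally, stress load and recovery are assessed by physiological measurements".
- **Statistical Analysis.** "The data of the practitioners will be mainly analyzed descriptively due to the small sample size". The next sentence reads: "Interferential statistics will be used to identify group differences". One two-sided threshold of 0.05 closes the section and covers everything in it. Multivariate analysis of variance is assigned to the patient data only.
- **Abstract, Methods.** "Intervention effects in both groups (practitioners and patients) will be evaluated separately using multivariate variance analysis". On the practitioner measures it says: "Primary and secondary outcomes are measured by physiological parameters (heart rate variability, saliva cortisol) and validated questionnaires". It places these assessments at M1, M2 and M3.
- **Abstract, Discussion.** "This study evaluates the effectiveness of two stress management intervention programs for patients and practitioners within cardiac catheter laboratory". The main Discussion repeats the aim for both populations.
- **Sample Size Determination.** Perceived stress is the main criterion in the patient calculation. No calculation was made for practitioners.
- **Visits.** Table 2 schedules PSS and TICS at M1 and M3 only, with M3 six months after M1. Study Design uses the label M3 for both the visit after the 8-week programme and the 6-month visit.

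**The concern.** The practitioner study is a separate randomised trial with its own effectiveness question. It has two primary outcomes of equal standing, one unadjusted threshold and no power calculation that would single out one of them. A significant arm difference on PSS alone or on TICS alone could therefore be reported as showing that the programme works, and the stated 5% would not describe the risk of a false claim.

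The article also gives two accounts of the analysis behind such a claim. One is a multivariate test; the other is a mainly descriptive analysis with unspecified group tests. The accounts differ in error rate and in what a significant result would mean. The visit at which the primary outcomes are compared is unclear as well, because the abstract, Study Design and Table 2 do not agree.

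**Working it through.** **No figure to reproduce.** The article states no sample size, power or familywise error rate for practitioners.

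**Inputs**
- Number of primary outcomes: k = 2, PSS and TICS (Outcomes).
- Level for each test: 0.05 two-sided, critical value c = 1.96 (Statistical Analysis).
- Success rule: not given. Assumed: success if either outcome is significant.
- Correlation r between the two test statistics: not given. Range taken: 0 to 0.9.

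**Step 1, uncorrelated outcomes.** Risk of at least one false positive = 1 − (1 − 0.05)² = 1 − 0.9025 = 0.0975.

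**Step 2, correlated outcomes.** For normal test statistics with common correlation r,

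risk = 1 − ∫ a(x)^k φ(x) dx, with a(x) = Φ((c − √r·x)/√(1 − r)) − Φ((−c − √r·x)/√(1 − r)).

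Numerical integration with k = 2 gives:

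| r | Risk if either may win |
|---|---|
| 0 | 9.75% |
| 0.3 | 9.5% |
| 0.5 | 9.1% |
| 0.7 | 8.4% |
| 0.8 | 7.8% |
| 0.9 | 7.0% |

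Relative to the stated level, this is 7.0/5 = 1.4 times to 9.75/5 = 1.95 times.

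**Step 3, rules that would hold 5%**
- One named primary contrast at 0.05: 5%. Testing TICS only after a significant PSS result adds nothing when neither outcome differs, because a false claim still has to begin with PSS.
- Bonferroni, 0.025 each: 1 − 0.975² = 0.0494 if independent, and at most 5% otherwise.
- Both outcomes required: at most 5%.
- One prespecified multivariate test of PSS and TICS at 0.05: 5% when neither outcome differs.

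**Step 4, what the text says about the deciding analysis**

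| Place | Practitioner analysis |
|---|---|
| Abstract, Methods | Multivariate analysis of variance, as for patients |
| Statistical Analysis | Mainly descriptive, plus inferential tests of group differences; multivariate analysis named for patients only |

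The first account could hold 5%. The second, applied to each primary outcome in turn, gives the risks in Step 2.

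**Step 5, the visit**

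| Place | Post-baseline visit for PSS and TICS |
|---|---|
| Table 2 | M3 only, 6 months after M1 |
| Abstract, Methods | Primary and secondary outcomes at M2 (after the programme) and M3 (6 months) |
| Study Design | Label M3 attached to both the 8-week and the 6-month visit |

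As Table 2 stands, there is one post-baseline comparison per primary outcome, so the family is two tests.

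**The case against.** **The inflation depends on an assumed rule.** Nothing in the article says that either outcome is enough. If both are required, or if the abstract's multivariate test covers PSS and TICS jointly, there is no excess when neither outcome differs. This stands, and the 7% to 9.75% is therefore conditional. It does not settle the matter, because the one sentence that could supply a joint test conflicts with Statistical Analysis.

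**The practitioner analysis is mainly descriptive and unpowered.** This weakens a confirmatory reading. It does not remove it, since group tests, a 0.05 threshold and an effectiveness aim all remain.

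**Success rules and multiplicity methods usually sit in the analysis plan or full protocol.** That is fair, and their absence from an article is not the point here. The point is what the article does state: two equal primary outcomes, one common threshold, and accounts of analysis and visits that do not agree.

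**Stronger readings the text does not support.**
- A reader might take about 9% as a minimum. It is not: two stress scales may be strongly correlated, and the risk is then 7% to 8.4% for r from 0.9 to 0.7.
- A reader of the abstract might count HRV and cortisol as further primary outcomes, which would give 1 − 0.95⁴ = 18.5% for four independent tests. The abstract's sentence covers primary and secondary outcomes together without sorting them. Outcomes lists the physiological measures as additional, and Statistical Analysis plans to compare them within individuals. Larger families built from several markers and day types have still less basis.

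**Conclusion.** The concern holds in a limited form. With two unranked primary outcomes each tested at two-sided 0.05, the risk of a false effectiveness claim for practitioners is about 7% to 9.75% instead of 5%, **if** either outcome may carry the claim. The position within that range depends on a correlation the article does not give, and the calculation treats the test statistics as jointly normal. HRV and cortisol are not part of this family.

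Separately, and without any assumption, the article contradicts itself on whether practitioners receive a multivariate analysis. It also contradicts itself on which visits carry the primary outcomes. Both need settling before a practitioner result can be interpreted, and the point should be addressed before analysis. It does not invalidate the trial.

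**What to change.** - **Outcomes and Statistical Analysis:** name one primary contrast for practitioners, the between-arm difference in PSS at the post-baseline visit that Table 2 schedules (M3, 6 months). Test TICS at 0.05 only if PSS is significant.
- **Statistical Analysis:** state that all other practitioner p-values are descriptive, and report those outcomes as estimates with 95% confidence intervals. This fits the mainly descriptive intent already stated.
- **Abstract:** align the statements on practitioner analysis and on primary and secondary outcomes with the above.
- **Abstract and Study Design:** reconcile the visit labels with Table 2, so that the 8-week and 6-month visits have different names and the visit for PSS and TICS is the same throughout.

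Putting PSS before TICS is a choice. A Bonferroni split at 0.025 each, or one prespecified multivariate test of the two, would also hold 5% when neither outcome differs. Whichever rule is taken must be stated.

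The cost is wording in a few sections and no extra data. Since Study Status reports that the first participants have been assessed, the change should be dated and made before any comparison of the arms. The price is that a significant TICS or biomarker result without a PSS effect could no longer be claimed as effectiveness.

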### Data Management

The study is conducted in compliance with the EU's General Data Protection Regulation (GDPR) (60). All collected data will be processed pseudonymized. After completion of data collection all data will be anonymized for data analysis. Compliance with data protection is ensured by strictly anonymized data input into electronic data base. Personal data will be collected on the day of the recruitment by a member of the research group. This data will be assessed in written form and stored in a secured case with restricted access during the whole project.

### Statistical Analysis

All statistical analyses will be performed using SPSS. The data of the practitioners will be mainly analyzed descriptively due to the small sample size. Interferential statistics will be used to identify group differences. A comparison with norms of the German general population will be performed to assess the stress of the practitioners in the cardiac catheter laboratory. Baseline and post-interventional physiological data like circadian profile slopes of HRV and derived indicators (SDNN, RMSSD, number and percentage of R-R intervals lower or >50 msec) as well as saliva cortisol, alpha-amylase and lysozyme measurements will be compared on an intraindividual level. The data of the patients will be analyzed according to a multivariate variance analysis (between-subject factor: intervention group vs. control group). Sociodemographic data, sedative medication, adherence to the intervention will be implemented as control variables or stratification variables for subgroup analysis. Statistical significance is set at *p* < 0.05 (two-sided) and effect sizes will be reported.

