## Methods and Analysis

### Study Design

The multicenter study “Heartbeat” implement a randomized and controlled pre-post-study design involving two intervention trials with parallel groups, for patients with elective cardiac catheterization and practitioners at the catheterization lab, respectively (Figure 1, DRKS No: 00026624^1^). The patient study with a 1:1 randomization by person and a standard treatment control group involves three measurement points: the day before (M1 = admission day) and the day after the video-based stress management intervention and cardiac catheterization examination (M2 = CC examination day), and 6 months after baseline (M3). The MBSR intervention trail for the practitioners at the CC lab involves a 1:1 randomization by group and a no-treatment control group with three measurement points: before (M1) and after the 8-week (M3) intervention with a mindfulness-based stress reduction program, as well as 6 months after baseline (M3). The study takes place at the two clinic sites of the Ernst-von Bergmann community clinic, in Potsdam (patients and practitioners) and Bad Belzig (only patients). The time of data collection is estimated with ~1 h for all questionnaires and 2 days for the physiological measurements (practitioners). The data collection period is planned from 01/2021 to 12/2022.

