
Both stress-management intervention for patients and practitioners are expected to have beneficial effects on the involved individuals. We expect to significantly minimize tension, perceived stress during the cardiac catheterization in patients of the intervention group. Additionally, we expect a favorable effect on physiological outcome like heart rate, blood pressure (in patients) and heart rate variability (in practitioners). An effective stress reduction should be favorable for the individual patients but it should further prevent complications and stressful incidents during the cardiac catheterization. On this account a successful patient intervention may add to less hazard and more safety in the workplace, improved working conditions and occupational safety, preservation of earning capacity, avoidance of participation restrictions and loss of performance for the practitioners. These positive aspects of work safety for the staff members of the catheterization lab should additionally pay off for patient security and satisfaction. The study may add knowledge how to eliminate stressful exposures and to contribute to more (psychological) security, less output losses and exhaustion during work.

All evaluated guidelines, materials for the psychoeducational intervention in patients and MBSR intervention in practitioners should be transferred in clinical routines.

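### The one comparison specified for practitioner HRV and saliva measures is within-person before versus after; it is not tied to the randomised arms and does not fit the plan's other statements on practitioner effects

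*Protocol article*

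**What the plan says.** All places are in the protocol article.

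- **Design.** Under Study Design, the practitioner trial "involves a 1:1 randomization by group and a no-treatment control group with three measurement points". Table 2 schedules HRV and the saliva stress profile at M1 and M2.
- **Analysis of these measures.** Under Statistical Analysis, the sentence on physiology opens with "Baseline and post-interventional physiological data like circadian profile slopes of HRV and derived indicators" and ends "as well as saliva cortisol, alpha-amylase and lysozyme measurements will be compared on an intraindividual level". The arms are not mentioned in it.
- **Analysis of practitioner data in general.** The same section says "The data of the practitioners will be mainly analyzed descriptively due to the small sample size", followed directly by "Interferential statistics will be used to identify group differences", which names no outcome.
- **Abstract, Methods.** Directly after scheduling the practitioner biomarkers, it says "Intervention effects in both groups (practitioners and patients) will be evaluated separately using multivariate variance analysis".
- **Contrast with patients.** The next sentence of Statistical Analysis, on patients, does name intervention versus control as the between-subject factor.
- **Expectation.** In the Discussion, "we expect a favorable effect on physiological outcome like heart rate, blood pressure (in patients) and heart rate variability (in practitioners").
- **Standing of the measures.** Under Outcomes, the practitioner primaries are PSS and TICS; the physiological measures are introduced as additional.

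**The concern.** A within-person change from M1 to M2 contains any MBSR effect plus everything else that changes over about 8 weeks. The article itself points to several influences that could reach both arms:

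- the operative guideline hangs as a poster in the lab where control staff also work (its posting date is not given);
- the Introduction expects the two interventions to influence both patients and practitioners, so the patient video could affect all lab staff;
- HRV comes from a chest strap that staff put on themselves, so familiarity may change the readings.

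Season and caseload on the sampled days are further general candidates. The randomised control arm is there to subtract such shared change, yet the only comparison that names HRV and the saliva markers does not use it. The Discussion expects a favourable effect on practitioner HRV, and a before-after change in MBSR staff could not by itself support that statement. Finding significance in one arm and not in the other would not support it either, because that is not a test of the difference between arms.

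**Working it through.** **1. No plan figure to reproduce.** The article gives no practitioner number, effect size, SD or power; under Sample Size Determination it says that none was required for this group. The size of the problem therefore has to be shown over assumed ranges.

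**2. Statements side by side.**

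| Place | Data named | Comparison stated |
|---|---|---|
| Statistical Analysis, physiology sentence | HRV slopes and indicators, saliva markers | Baseline vs post, within person |
| Statistical Analysis, sentence after the descriptive one | None named | Group differences, inferential |
| Abstract, Methods | Practitioners and patients, no outcome named | Variance analysis of intervention effects |
| Statistical Analysis, patient sentence | Patient data | Intervention vs control as between-subject factor |

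Only the first row names the practitioner biomarkers, and it is the row without an arm contrast.

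**3. Inputs for the calculation.**

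- Two-sided significance level 0.05 (Statistical Analysis).
- Assumed: n = 8, 10, 15 or 20 per arm.
- Assumed: the same drift in both arms, 0.3 or 0.5 SD of the change score.
- Assumed: no MBSR effect, and normal, independent change scores.
- Assumed: a paired t-test as the within-person comparison, since the article names no test.

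**4. Within-arm test.** With drift δ in SD units, the paired t statistic follows a noncentral t distribution with n − 1 degrees of freedom and noncentrality λ = δ√n. The rejection rate is P(|T| > t with n − 1 df at 0.975). For example, n = 8 and δ = 0.3 give λ = 0.3 × √8 = 0.849 and a critical value of 2.365, hence a rate of 0.114. For n = 20 and δ = 0.5, λ = 0.5 × √20 = 2.236, the critical value is 2.093 and the rate is 0.565.

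**5. Between-arm test.** With equal drift, the expected difference in change is δ − δ = 0, so a two-sample t-test of change keeps its nominal level. A simulation of 40,000 replicates per scenario checked both tests:

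| n per arm | Drift (SD of change) | Within-arm, noncentral t | Within-arm, simulated | Between-arm, simulated |
|---|---|---|---|---|
| 8 | 0.3 | 0.114 | 0.116 | 0.051 |
| 8 | 0.5 | 0.232 | 0.236 | 0.050 |
| 10 | 0.3 | 0.136 | 0.137 | 0.050 |
| 10 | 0.5 | 0.293 | 0.293 | 0.050 |
| 15 | 0.3 | 0.191 | 0.189 | 0.050 |
| 15 | 0.5 | 0.438 | 0.441 | 0.050 |
| 20 | 0.3 | 0.247 | 0.249 | 0.049 |
| 20 | 0.5 | 0.565 | 0.566 | 0.050 |

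With no drift, the within-arm rate is 0.048 to 0.051, so the excess comes from shared change alone.

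**6. Price of the between-arm contrast.** For a common SD of change, the standard error is SD/√n within an arm and SD × √(2/n) between arms, a ratio of √2 = 1.41. With t quantiles, the 95% half-widths are 0.836 vs 1.072 SD at n = 8 and 0.468 vs 0.640 SD at n = 20, that is 28% and 37% wider.

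**The case against.** The strongest defence is that the article does announce a between-arm analysis for practitioners. The abstract promises a variance analysis of their intervention effects straight after mentioning the biomarkers, and Statistical Analysis promises tests of group differences straight after the practitioner sentence. Neither excludes HRV or saliva. Nor does an intraindividual comparison rule out an arm contrast: HRV and cortisol profiles differ widely between people, so computing each person's change first and then comparing changes between arms would be sensible. Practitioner data are to be mainly descriptive, the biomarkers are not primary, and a condensed article may leave the exact model to a fuller document.

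Much of this stands. A reader might infer that the arm comparison has been dropped for the biomarkers, or that any drift will be reported as an MBSR effect. The documents support neither: no sentence drops the control arm, and none says that a within-person change will be taken as the intervention effect. The drift figures are also hypothetical, and at a drift of 0.3 SD the paired test would miss the drift in about 75% to 89% of trials.

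The mismatch remains. A detail left open would be no finding, but this section does state a comparison for these measures, and it is one that cannot isolate the intervention effect. The sentences that could repair it name no outcome, and the article never says that individual changes will be compared between arms.

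**Conclusion.** The point holds as a lack of fit that needs reconciling. The specified comparison for practitioner HRV and saliva measures is within-person only. It is not linked to the randomised arms, and it does not sit with the group-difference sentence beside it or with the abstract. Used alone, it confounds MBSR with change shared by both arms.

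Under the assumed figures, a paired test in the MBSR arm would be significant in about 11% to 57% of trials with no MBSR effect, against about 5% for the between-arm test. These rates depend on an assumed arm size, an assumed drift, independent persons and a paired test as decision rule; none of these comes from the article. The importance is moderate: the correction should be made, but PSS and TICS, the practitioner primaries, are not covered by the criticised sentence.

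**What to change.** In Statistical Analysis, consistent with the abstract, state that the intervention effect on each practitioner HRV and saliva measure is the between-arm contrast of M1-to-M2 change, estimated either as M2 adjusted for M1 or as the group-by-time term, with a 95% confidence interval. The interval should respect the unit randomised, since Study Design describes allocation by group. Report within-person change for both arms as description only.

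The cost is wording, plus an interval about 28% to 37% wider than the within-person one under the assumptions above, and wider still if the randomised groups induce correlation. No additional measurement is needed, because the design already provides a control arm and Table 2 already schedules these measures at M1 and M2.

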### Sample Size Determination

We calculated the sample size for two patient groups for two measurement points based on a pilot study. The sample was powered to assume a medium effect size (*d* = 0.25) and a minimum detectable clinical difference of 0.5 standard deviation on the (z-standardized) main criterion: perceived stress. For the main criterion, the power for significant group differences is 1-β = 0.93 with a case number of *N* = 60 people per group (38). As the sample for the practitioners was limited to all members of the catheterization lab of the clinic who fulfill the inclusion criteria, a sample size determination was not required.

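### The statistical section specifies no model with both baseline (or time) and randomised arm, its single MANOVA does not suit the listed patient primary outcomes, and practitioner physiology is specified only as a within-person comparison

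*Protocol article*

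**What the plan says.** All references are to the protocol article.

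- **Study Design.** The trial is said to "implement a randomized and controlled pre-post-study design", with two parallel-group trials. Patients are randomised 1:1 by person against standard treatment. Practitioners are randomised 1:1 by group against no treatment.
- **Sample Size Determination.** The patient trial is sized for two groups at two measurement points on perceived stress, using "The sample was powered to assume a medium effect size (*d* = 0.25") and "a minimum detectable clinical difference of 0.5 standard deviation". The stated result is "1-β = 0.93 with a case number of *N* = 60 people per group".
- **Outcomes.** "The primary outcomes for patients are reduced complications and less sedative medication during CC", followed by physiological strain, PSS and POMS. For practitioners the primary outcomes are PSS and TICS, and physiology is assessed in addition.
- **Table 1 (patients).** PSS is taken at M1 and M3, POMS at M1 and M2. **Table 2 (practitioners).** Heart rate variability and saliva markers are taken at M1 and M2.
- **Statistical Analysis, patients.** "The data of the patients will be analyzed according to a multivariate variance analysis (between-subject factor: intervention group vs. control group"). The control or stratification variables are sociodemographic data, sedative medication and adherence.
- **Statistical Analysis, practitioners.** The data are to be analysed mainly descriptively, with inferential statistics for group differences and no model named. For baseline and post-intervention heart rate variability and saliva markers, the "measurements will be compared on an intraindividual level".
- **Abstract.** Multivariate variance analysis is named for intervention effects in both populations, analysed separately.

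**The concern.** The design collects a baseline and randomises, yet no sentence describes a model that uses both. Three consequences follow.

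1. **Patients, precision.** The section names the method, the factor and the control variables. The list leaves out the M1 score, usually the most informative covariate for a questionnaire outcome. Followed literally, the analysis has less power than the data allow.
2. **Patients, fit of the method.** MANOVA models a vector of continuous, jointly observed responses. Complications and sedative use are events or counts. The only occasion that PSS and POMS share is M1, before the intervention. A joint post-intervention vector would have to pair ward data at M2 with postal data at M3, and anyone missing either would drop out.
3. **Practitioners, control.** A before-after change within a person mixes any MBSR effect with season, workload, habituation to sampling and regression to the mean. The no-treatment arm exists to remove these, but the sentence on physiology does not use it.

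**Working it through.** **Inputs from the document:** 60 per arm; a 0.5 SD difference; two-sided alpha 0.05 ("Statistical significance is set at *p* < 0.05 (two-sided) and effect sizes will be reported"); stated power 0.93. **Not given, so assumed:** the correlation r between M1 and post scores; for practitioners, the number tested, r and the common drift.

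**Step 1. The plan's own 0.93.** A two-sample t test on the post score alone has noncentrality 0.5 × √(60/2) = 2.739 on 118 df, giving power 0.775. With d = 0.25 it is 0.27. Neither is 0.93. The figure can be reached in three ways, each with a correlation that the article does not state:
- 0.25 read as Cohen's f (f = d/2 for two equal groups, so d = 0.5) in a two-time-point repeated-measures test of the between-subject effect: 0.94 at r = 0.2, 0.92 at r = 0.3.
- 0.5 SD with M1 as covariate: 0.92 at r = 0.6.
- 0.5 SD in a change-score (arm-by-time) test: 0.94 at r = 0.7.

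All three use the baseline measurement. The 0.93 is therefore not shown to be wrong, but a post-only arm comparison does not deliver it.

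**Step 2. Gain from M1 as covariate.** The residual SD becomes √(1 − r²), so the F test (1, 117 df) has noncentrality λ = 30 × 0.25/(1 − r²).

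| r (assumed) | λ | Power |
|---|---|---|
| M1 not used | – | 0.775 |
| 0.3 | 8.24 | 0.81 |
| 0.5 | 10.00 | 0.88 |
| 0.7 | 14.71 | 0.97 |

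**Step 3. If time is meant to be in the model.** Naming only the between-subject factor is still not enough. If the 0.5 SD effect exists only after the intervention, the arm difference averaged over M1 and the post score is 0.25 SD, so f = 0.125. Then λ = f² × 120 × 2/(1 + r), which is 3.125 at r = 0.2 and 2.88 at r = 0.3, and power is 0.42 and 0.39. The treatment effect would be the arm-by-time term, which is not named.

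**Step 4. Joint modelling of the primary outcomes.** From Table 1, PSS is at {M1, M3} and POMS at {M1, M2}. The intersection is {M1}, so no post-intervention occasion carries both. Complications and sedative use are recorded at the procedure and have no M1 value, so baseline adjustment does not apply to them.

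**Step 5. Within-person comparison of practitioner physiology (illustration).** Suppose MBSR has no effect and everyone drifts by δ SD between M1 and M2, with r = 0.6. The standardised paired shift is δ/√(2(1 − 0.6)): 0.224 for δ = 0.2 and 0.335 for δ = 0.3. Rejection rates of a two-sided 5% paired t test:

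| n tested | δ = 0.2 | δ = 0.3 |
|---|---|---|
| 10 | 10% | 16% |
| 15 | 13% | 23% |
| 20 | 16% | 30% |

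A between-arm contrast removes a drift that is common to both arms.

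**The case against.** **The article is silent on M1; it does not exclude it.** Calling a factor between-subject is natural wording when a within-subject time factor is also planned. The design is called pre-post, the sample size counts two measurement points, PSS is measured at exactly two, and 0.93 is reached only by models that use baseline. This stands. A reader might infer that M1 will be left out, and the text does not support that. What remains is that the section lists factor and covariates without baseline or time, and so does not match the article's own sample-size basis.

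**The practitioner control group is not discarded.** The same section announces inferential statistics for group differences, the Abstract applies variance analysis to practitioners too, and the physiological measures are additional to the primary outcomes. This also stands: a reader might infer that the control arm will be ignored, and the documents do not say so. But the general sentence does not tie an arm contrast to heart rate variability or saliva markers, and the sentence that deals with those measures gives only a within-person comparison.

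**Omitting M1 does not bias the patient comparison.** Correct. The cost is precision, and at r = 0.3 it is only about 4 percentage points.

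**No sentence puts all outcomes into one MANOVA.** The loss to incomplete cases cannot be quantified from the article. Five independent outcomes, each 90% complete, would keep 0.9⁵ = 59% of patients, but fully overlapping missingness would keep 90%. No retention figure should be claimed. The mismatch in data type and timing holds regardless, because the method is stated for the patient data without exception.

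**Model terms are often left to an analysis plan.** True of detail. Here the article does fix a method, a factor and a covariate list, and these are what need correcting.

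**Conclusion.** The point holds in this form: no stated model contains both baseline (or time) and arm, although design and sample size are pre-post. For patients the consequence is lost precision, with power 0.775 against 0.81 to 0.97 at 60 per arm and 0.5 SD, over assumed correlations of 0.3 to 0.7. The comparison stays valid under randomisation. That a single MANOVA does not suit event or count outcomes, or PSS and POMS with no shared post-intervention time point, rests on the article's own outcome list and Table 1 and needs no assumption. For practitioner physiology, the comparison as specified cannot by itself support a conclusion about MBSR. The 10% to 30% rejection rates only illustrate this and depend wholly on the assumed n, correlation and drift. The point does not extend to saying that M1 or the practitioner control arm has been excluded.

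**What to change.** **Patients.** Analyse each continuous outcome measured at M1 by ANCOVA, or by a mixed model using all available data, with arm, M1 value and site. Name the time point for each outcome (M3 for PSS, M2 for POMS). Analyse complications and sedative use by a binary or count method, reporting a risk difference or rate ratio with no M1 term. State the correlation and model behind the 0.93 so that sample size and analysis match.

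**Practitioners.** For heart rate variability and saliva markers, report the between-arm difference at M2 adjusted for M1 with a 95% CI. If whole groups were allocated, as randomisation by group may mean, the analysis must reflect that; a random person effect alone would not. Keep intraindividual change as description.

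**Cost.** A revision of the statistical section and a little more analysis work. The measurements are already scheduled, the methods are available in SPSS, and no new data are needed.
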